### Study design

This study is an investigator-blinded randomised controlled trial of BCG vaccination given at birth versus BCG vaccination given at 6 weeks of age. Cord blood and two venous blood samples will be collected from participants to allow comparison of innate immune system parameters. All participants will be clinically followed-up until 10 completed weeks of age, to allow comparison of illness outcomes. This study design will allow comparison of outcomes between BCG-naïve and -vaccinated infants up to 6 weeks of age, and early with delayed BCG-vaccinated infants from 6 to 10 weeks of age, helping to identify whether there is a critical period for BCG-induced non-specific effects. The time-point of 6 weeks for the delayed BCG group has been chosen as it is the longest delay possible prior to the potential confounding influence of primary immunisations.

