### Intervention and randomisation

All infants will receive 0.05 ml of BCG-Statens Serum Institute (SSI, Copenhagen, Denmark) (Danish Strain 1331) intra-dermally into the right deltoid. This will be given either at birth (Early intervention arm) or at 6 weeks of age (Delayed intervention arm).

Intervention and blood sampling time-point allocation will be determined by block randomisation, stratified by sex. This will be carried out by an independent statistician, prior to the trial commencement, using Stata (StataCorp, College Station, TX, USA) to generate the allocation sequence. Allocations will be concealed within sequentially numbered, sealed opaque envelopes, prepared by two research assistants who are independent of the trial. Upon delivery of an eligible infant, assignment of allocation will be carried out by midwives who will select the next sequential envelope according to the infant’s gender.

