### Blinding

This study will be single blind. Mothers will not be blinded to intervention allocation due to lack of feasibility (BCG produces a visible reaction) and to reduce confusion if a child who is lost to follow-up presents to a community immunisation clinic.

Staff involved in administering BCG immunisation to the participants, either at birth or at 6 weeks of age, will not be involved in clinical follow-up or assessment of outcomes.

Investigators performing clinical assessment of children will be blinded to intervention allocation by means of a plaster placed over the area corresponding to BCG vaccination site. This will be placed by a nurse not involved in clinical assessment, prior to physician assessment. If a child is presenting due to concerns about the immunisation site it will be left uncovered and the un-blinding documented. Illness events arising from concerns or complications directly related to the BCG immunisation will not be included in the analysis of illness events, but will be presented separately.

Immunological investigations will be conducted on blood samples identified only by study number. The intervention allocation code will only be broken once laboratory analysis is complete and the data have been cleaned and locked.

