### Study procedures

#### Overview

Figure 1 shows the SPIRIT (Standard Protocol Items: Recommendations for Interventional Trials) diagram for the trial procedures. On presentation to labour ward, mothers in active labour will be screened for their eligibility and informed consent will be taken. Following delivery the infant will be assessed for eligibility and placental cord blood collected. Infants who are eligible for the study will be randomised as described above, to receive BCG vaccination either immediately or at 6 weeks of age. All infants will be followed-up until 10 completed weeks of age. During this time 2 × 2 ml venous blood samples and 2 stool samples will be collected and all routine immunisations will be given (Oral Polio Vaccination (OPV) at birth and primary immunisations at 6 and 10 weeks of age). Clinical follow-up of the infants will be carried out by weekly telephone interviews to check the well-being of participants, and physician review and anthropometry at each routine clinic visit for blood samples/routine immunisations (on average four visits per participant). Unwell participants presenting to the study clinic or Entebbe Grade B hospital will also be reviewed and managed by the study team, free of charge. Study follow-up is complete once the child has completed 10 weeks of age.

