### Ethics

As this trial will alter the timing of BCG from the current Ugandan guidelines (BCG at birth) in half of the study infants, a thorough risk-benefit analysis of a 6-week delay in vaccination has been conducted. In summary, we feel that the risks of delay are minimal for the following reasons:Neonatal TB is rare and the chances of infants in the delayed BCG arm becoming infected during a 6-week delay period are extremely small. At least 7 previous studies have been conducted in areas of high TB prevalence that randomised infants to delayed BCG vaccination past 6 weeks of age [19-24]. None of these studies showed an increase in TB incidence in the delayed vaccination group either in the period prior to vaccination or during follow-up (cumulative n for delayed BCG vaccination = 849, median follow-up time 1 year).A recent study using an Entebbe based birth-cohort showed a prevalence of latent TB infection of 9.7% in children under 5 years old [52]. This suggests that in our population, a 6-week delay in BCG administration risks 0.63 infants becoming infected with latent TB. However, the strongest risk factor for latent TB acquisition in Entebbe is a known contact with a TB case (odds ratio (OR) 2.62 (1.29 to 5.30), unpublished data). Thus, the exclusion of infants at risk of TB from mother or a household contact will reduce this risk to negligible. Active weekly follow-up of infants will occur to ensure they remain healthy and the trial will be stopped early if cases of TB are found to be higher in the delayed BCG arm.

There is also evidence that delay in BCG vaccination from birth to 6 weeks may be beneficial for participants because:The optimal timing of BCG vaccination for immunity against TB is not known. There is some evidence that delaying BCG past the neonatal period may improve the magnitude and duration of anti-TB immunity, thus providing direct benefit to participants in the delayed vaccination arm [19-24].The incidence of vaccination-induced complications, including BCG-induced abscesses, suppurative lymphadenitis and osteomyelitis are reduced by approximately one third in infants who receive BCG vaccination after the neonatal period [21].

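### Follow-up ends at age 10 weeks in both arms, so BCG complications are observed for about 10 weeks after vaccination in the Early arm and about 4 in the Delayed arm; any by-arm presentation should use the window both share

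*Protocol article*

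**What the plan says.** Under Intervention and randomisation, the protocol article sets the time of BCG by arm: "This will be given either at birth (Early intervention arm) or at 6 weeks of age (Delayed intervention arm"). Study design ends observation by age, not by time since vaccination: "All participants will be clinically followed-up until 10 completed weeks of age". The Overview of study procedures confirms that nothing later is planned: "Study follow-up is complete once the child has completed 10 weeks of age". Study design also describes the second part of the trial as a comparison of "early with delayed BCG-vaccinated infants from 6 to 10 weeks of age".

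The Blinding section deals with vaccine-related events as follows: "complications directly related to the BCG immunisation will not be included in the analysis of illness events, but will be presented separately". It gives no denominator, time window or comparison for that presentation. The Ethics section, arguing that delay may benefit participants, cites an external study for the statement that abscesses, suppurative lymphadenitis and osteomyelitis caused by the vaccine "are reduced by approximately one third in infants who receive BCG vaccination after the neonatal period".

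Study limitations recognises that at 10 weeks the Delayed arm has had BCG more recently, but only for the immune comparison. The longer follow-up mentioned there is still unfunded, and its stated purpose is to clarify immune effects, not safety.

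**The concern.** A stopping rule based on age gives each arm a different length of observation after the injection. A complication that appears 4 to 10 weeks after BCG can be recorded in the Early arm but not in the Delayed arm. If the separately presented events are tabulated by arm as they stand, the two columns cover different periods of risk, and the difference can only lower the expected Delayed-arm count relative to the Early arm.

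That is also the direction of the result cited in the Ethics section. A reader who sees fewer complications in the Delayed column could take it as support for that result, although shorter observation may have produced some or all of the gap. The later Delayed-arm events cannot be recovered by analysis, because they are never collected. What can still be settled is how the collected events are set side by side.

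**Working it through.** The document gives no complication rate, onset time or power for safety, so there is no planned figure to reproduce. The check has four steps.

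**1. Observation after BCG.** Inputs: end of follow-up at age 10 weeks (Study design, Overview); BCG at age 0 or 6 weeks (Intervention and randomisation); 560 infants, half of them in the Delayed arm (Sample size considerations, Ethics), so 280 per arm.

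- Early: 10 − 0 = 10 weeks, or 280 × 10 = 2,800 infant-weeks with no loss.
- Delayed: 10 − 6 = 4 weeks, or 280 × 4 = 1,120 infant-weeks.
- Ratio of windows: 4/10 = 0.40.

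Table 1 describes the last sample as three weeks after the 6-week intervention, while Table 2 places it at 10 weeks of age. The 4 weeks used here follow from the ages and agree with Study design and Table 2.

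**2. Expected ratio of crude counts under equal true risk.** Let F(t) be the share of complications that have appeared by t weeks after BCG, the same in both arms. The expected Delayed/Early ratio is F(4)/F(10). This equals 1 − s, where s is the share of the complications seen by week 10 that arise after week 4. F is not in the document. For an assumed exponential onset with median m weeks, F(t) = 1 − exp(−t·ln 2/m):

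| Assumed median onset (weeks) | F(4) | F(10) | Expected ratio |
|---|---|---|---|
| 1 | 0.938 | 0.999 | 0.94 |
| 2 | 0.750 | 0.969 | 0.77 |
| 3 | 0.603 | 0.901 | 0.67 |
| 4 | 0.500 | 0.823 | 0.61 |
| 6 | 0.370 | 0.685 | 0.54 |
| 12 | 0.206 | 0.439 | 0.47 |
| 26 | 0.101 | 0.234 | 0.43 |

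Outside this family:

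- If every complication arises within 4 weeks, s = 0 and the ratio is 1.00.
- A constant hazard gives 0.40 (s = 0.6).
- Onset concentrated after week 4 would go lower; s = 0.75 gives 0.25.
- If s is one third, the ratio is 0.67, so truncation alone would look like a one-third reduction.

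**3. Chance.** Events may be few. Treat the counts as Poisson and assume a 10-week risk of 5% in the Early arm (280 × 0.05 = 14 expected events). The probability that the Delayed arm shows strictly fewer events is then 46% at ratio 1.0, 73% at 0.75 and 97% at 0.40. At an assumed 2% (5.6 expected) it is 44%, 61% and 85%. Both risks are assumptions.

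**4. Possible corrections.** Restricting both arms to the first 4 weeks gives F(4)/F(4) = 1.00 for any onset distribution, provided ascertainment in that window is equal. A rate per infant-week divides the count ratio by 0.40. That returns 1.00 only when the hazard is constant (0.40/0.40). If all complications arise within 4 weeks, it gives 1.00/0.40 = 2.5, an error in the opposite direction. A rate is therefore not a safe substitute for a common window.

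**The case against.** The strongest reply is that no comparison of complications between arms is planned. They are not among the aims or the primary or secondary outcomes, and the Statistical analysis section gives no test for them. The sentence under Blinding protects the illness outcome and does not set up a safety contrast. Follow-up to a common age suits the trial's main purpose, which is to compare infants of the same age. The layout of safety tables is commonly left to an analysis plan, and a condensed article cannot be faulted for silence on it. All of this stands, and it limits the point to how separately presented events should be shown if they are shown by arm. It does not remove the unequal window, which comes from a stated rule and not from silence.

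A reader might infer more: that the trial will show fewer complications with delay even if the risk is identical, or that its counts are set up to confirm the one-third reduction in the Ethics section. The document supports neither. The first needs some complications to arise 4 to 10 weeks after BCG, and no onset data are given; with few events, chance can also reverse the observed order. The second treats a cited external result, used in a risk-benefit argument, as though it were a trial hypothesis. Nor does the document show that most of the Delayed arm's risk period goes unobserved, since that too depends on the unknown onset distribution.

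**Conclusion.** The point holds in conditional form. The unequal windows, about 10 weeks against about 4, follow directly from the protocol's own rules. If complications are presented by arm as crude counts, the Delayed arm is expected to be under-counted to the extent that complications arise after week 4, and the bias cannot run the other way. Under equal true risk and equal ascertainment, the expected ratio may be anywhere from 1.00 (no bias) through 0.94 to 0.43 (exponential onset, median 1 to 26 weeks) to 0.40 (constant hazard). The document does not allow a choice within that range. No planned outcome analysis is affected; this is an inexpensive improvement to how a set of safety events is reported.

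**What to change.** Add to the Blinding section, where separate presentation is introduced, that any by-arm presentation of BCG complications will use time since vaccination over the window both arms share, the first 4 weeks after BCG. Early-arm events after week 4 should be listed separately and not contrasted with the Delayed arm.

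The text should also state two limits:

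- Scheduled contacts within the shared window differ. Weekly telephone calls run in both arms. In the Delayed arm, however, the window ends at the 10-week immunisation visit with physician review, while in the Early arm the scheduled clinic contact in the first 4 weeks is the day-5 blood sample, for infants allocated to it.
- Complications arising more than 4 weeks after BCG are not observed in the Delayed arm.

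The cost is a few lines of text and a re-cut of data already collected. The downside is that later Early-arm events drop out of the contrast, although they remain in the listing. A single later telephone call to Delayed-arm families would not restore balance and is not recommended: reaching 10 weeks after BCG means age 16 weeks, so one recall would have to cover six weeks that the Early arm had covered by weekly calls.

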## Methods

### Setting and participants

Infants will be recruited on the day of birth from the maternity ward of Entebbe Grade B hospital, a government hospital located in Wakiso District in central Uganda. The region is populated mainly by semi-urban, rural and fishing communities. Neonatal mortality rates in Uganda remain high at 28/1,000 live births, with a large proportion attributable to invasive infectious diseases.

### Eligibility criteria

The inclusion criteria for this study are:Infant of a gestational age and birth weight sufficient to allow discharge directly home from hospital without requirement for supplemental oxygen or feedingDelivery sufficiently uncomplicated to allow discharge directly from hospital without inpatient managementHIV-negative mother (based on antenatal records)Residence within the study catchment areaConsenting mother

No specific weight or gestational age limit has been set for this study. Clinical responses to early BCG are suggested to have the greatest effect in infants of the lowest birth weight [18]; thus, it is important to include these infants in data collection. No increased rate of detrimental side-effects or reduction of immunological efficacy has been shown with BCG immunisation of premature infants [48]. Written informed consent will be obtained from the mothers of all infants prior to their enrolment in the study.

Neonates will be excluded from the study if:Cord blood is not obtainedThey have major congenital malformationsThe infant is clinically unwell, as judged by a midwifeKnown maternal TB or active TB within the family (based on direct questioning of mother during recruitment)Maternal or family member positive for any of the following TB screening symptoms:Cough > 2 weeksRecent haemoptysis>3 kg weight loss in past monthRecurrent fevers/chills or night sweats for the past 3 days or more

### Intervention and randomisation

All infants will receive 0.05 ml of BCG-Statens Serum Institute (SSI, Copenhagen, Denmark) (Danish Strain 1331) intra-dermally into the right deltoid. This will be given either at birth (Early intervention arm) or at 6 weeks of age (Delayed intervention arm).

Intervention and blood sampling time-point allocation will be determined by block randomisation, stratified by sex. This will be carried out by an independent statistician, prior to the trial commencement, using Stata (StataCorp, College Station, TX, USA) to generate the allocation sequence. Allocations will be concealed within sequentially numbered, sealed opaque envelopes, prepared by two research assistants who are independent of the trial. Upon delivery of an eligible infant, assignment of allocation will be carried out by midwives who will select the next sequential envelope according to the infant’s gender.

### Blinding

This study will be single blind. Mothers will not be blinded to intervention allocation due to lack of feasibility (BCG produces a visible reaction) and to reduce confusion if a child who is lost to follow-up presents to a community immunisation clinic.

Staff involved in administering BCG immunisation to the participants, either at birth or at 6 weeks of age, will not be involved in clinical follow-up or assessment of outcomes.

Investigators performing clinical assessment of children will be blinded to intervention allocation by means of a plaster placed over the area corresponding to BCG vaccination site. This will be placed by a nurse not involved in clinical assessment, prior to physician assessment. If a child is presenting due to concerns about the immunisation site it will be left uncovered and the un-blinding documented. Illness events arising from concerns or complications directly related to the BCG immunisation will not be included in the analysis of illness events, but will be presented separately.

Immunological investigations will be conducted on blood samples identified only by study number. The intervention allocation code will only be broken once laboratory analysis is complete and the data have been cleaned and locked.

### Study procedures

#### Overview

Figure 1 shows the SPIRIT (Standard Protocol Items: Recommendations for Interventional Trials) diagram for the trial procedures. On presentation to labour ward, mothers in active labour will be screened for their eligibility and informed consent will be taken. Following delivery the infant will be assessed for eligibility and placental cord blood collected. Infants who are eligible for the study will be randomised as described above, to receive BCG vaccination either immediately or at 6 weeks of age. All infants will be followed-up until 10 completed weeks of age. During this time 2 × 2 ml venous blood samples and 2 stool samples will be collected and all routine immunisations will be given (Oral Polio Vaccination (OPV) at birth and primary immunisations at 6 and 10 weeks of age). Clinical follow-up of the infants will be carried out by weekly telephone interviews to check the well-being of participants, and physician review and anthropometry at each routine clinic visit for blood samples/routine immunisations (on average four visits per participant). Unwell participants presenting to the study clinic or Entebbe Grade B hospital will also be reviewed and managed by the study team, free of charge. Study follow-up is complete once the child has completed 10 weeks of age.

**Figure 1 Fig1:**
[figure not shown]
**Standard Protocol Items: Recommendations for Interventional Trials (SPIRIT) diagram of study procedures.**

### Consent

Sensitisation of parents to the study will occur during antenatal classes via posters, group discussions and during individual midwife-led consultations. Mothers will then be approached for consent by trained midwives when presenting in active labour to Entebbe Grade B hospital. The study will be explained in detail verbally and the information sheet provided (or read to illiterate mothers). Information sheets will be available in English and Luganda. Consent will also be taken to allow for storage of excess samples and use of data in future research studies. Although consent during labour is not optimal, it is necessary to enable cord blood collection. However, consent will be verbally reconfirmed with mothers following delivery prior to any intervention. This method of consent and recruitment has been piloted in the same hospital and shown to be an appropriate and successful method.

### Data collected

Demographic details, anthropometric measurements and socio-economic indices will be collected at enrolment including gender, gestational age, birth weight, occipito-frontal circumference and length, maternal age and parity, parental ethnicity, parental educational level attained, accommodation type and assets. Global Positioning System (GPS) co-ordinates of the participant’s home address will also be collected to aid follow-up.

During routine clinic visits anthropometric and vital sign measurements will be collected. All mothers will be interviewed about illness episodes in the participant since they were last seen in clinic and any current concerns. Physical examination findings will be documented.

A standardised illness episode case report form will be completed whenever a child presents unwell to the research clinic or paediatric ward at Entebbe Grade B hospital. This will include anthropometric and vital sign measurement, symptoms and signs, investigation results, final diagnosis and outcome.

All participants will be interviewed by telephone on a weekly basis by a fieldworker using a standardised case report form to ensure the health of the infant. Any infants for whom there are concerns will be reviewed in clinic. This intensive follow-up will enhance identification of clinical illness episodes, which are secondary outcomes for the study. More importantly, however, it will allow early identification and management of any cases of perinatal TB, particularly in the delayed intervention group. Any suspected or confirmed cases of TB occurring during the study will be reported to the ethics committees and Data Safety Monitoring Board (DSMB), who will decide whether the study needs to be stopped early for safety.

Direct electronic data entry will occur for all case report forms. This will be verified and optimized by co-documentation with paper case report forms at the beginning of the study. Data will be maintained in encrypted, password protected forms, to maintain confidentiality.

### Blood samples collected

All participants in the study will have 10 ml placental cord blood collected at birth; divided into 5 ml of heparinised and 5 ml of ethylenediaminetetraacetic acid (EDTA)-anticoagulated blood. They will then have 2-ml venous blood samples collected at 2 time-points between birth and their exit from the study at 10 completed weeks of age. Each sub-study has up to four possible time-points where blood samples are collected, but each infant will only be bled at two of these time-points (randomly allocated) to avoid undue stress for the baby and the mother. The time-points have been selected to enable interrogation of the changes to the innate immune system induced by BCG both acutely following vaccination and in the longer term. The timing of the blood samples in the iron sub-study differs slightly from those in the cytokine and epigenetic sub-studies (see Table 2). These differences are necessitated by the systemic nature of iron metabolism. As hepcidin is produced mainly in the liver this precludes analysis of iron metabolism following *in-vitro* non-specific stimulation. Thus, the iron sub-study will use routine primary immunisations as *in-vivo* non-specific stimuli and measure the resulting changes to iron parameters.

